## Abstract

**Background:**

Obsessive-compulsive disorder (OCD) is a debilitating and prevalent anxiety disorder. Although the basal ganglia and frontal cortex are the brain regions that are most commonly hypothesized to be involved in OCD, the exact pathophysiology is unknown. By observing the effects of proven treatments on brain activation levels, the cause of OCD can be better understood. Currently, the gold standard treatment for OCD is cognitive behavioral therapy (CBT) with exposure and response prevention. However, this is often temporally and geographically inaccessible, time consuming, and costly. Fortunately, CBT can be effectively delivered using the internet (electronically delivered CBT [e-CBT]) because of its structured nature, thus addressing these barriers.

**Objective:**

The aims of this study are to implement an e-CBT program for OCD and to observe its effects on brain activation levels using functional magnetic resonance imaging (MRI). It is hypothesized that brain activation levels in the basal ganglia and frontal cortex will decrease after treatment.

**Methods:**

Individuals with OCD will be offered a 16-week e-CBT program with exposure and response prevention mirroring in-person CBT content and administered through a secure web-based platform. The efficacy of the treatment will be evaluated using clinically validated symptomology questionnaires at baseline, at week 8, and after treatment (week 16). Using functional MRI at baseline and after treatment, brain activation levels will be assessed in the resting state and while exposed to anxiety-inducing images (eg, dirty dishes if cleanliness is an obsession). The effects of treatment on brain activation levels and the correlation between symptom changes and activation levels will be analyzed.

**Results:**

The study received initial ethics approval in December 2020, and participant recruitment began in January 2021. Participant recruitment has been conducted through social media advertisements, physical advertisements, and physician referrals. To date, 5 participants have been recruited. Data collection is expected to conclude by January 2022, and data analysis is expected to be completed by February 2022.

**Conclusions:**

The findings from this study can further our understanding of the causation of OCD and help develop more effective treatments for this disorder.

**Trial Registration:**

ClinicalTrials.gov NCT04630197; https://clinicaltrials.gov/ct2/show/NCT04630197.

**International Registered Report Identifier (IRRID):**

PRR1-10.2196/30726

## Introduction

### Background

Obsessive-compulsive disorder (OCD) is a debilitating anxiety disorder that can manifest in a multitude of ways in individuals. The 1-year prevalence of OCD in Canada is estimated to be 1%, with approximately 3% of the population developing OCD at some point in their lifetime [1,2]. Although OCD is a relatively widespread disorder, there have been no conclusive results to date regarding its etiology [3,4]. By understanding the pathophysiology of OCD better, more targeted treatments can be developed, leading to higher effectiveness in symptom reduction.

OCD is categorized as having obsessions and compulsions that an individual is unable to control. These obsessions, uncontrollable thoughts, impulses, and ideas are found to be disturbing and anxiety-inducing by the individual. These obsessive thoughts and/or feelings typically manifest in the impaired control of mental activities, thoughts related to uncertainty, sex, violence, or contamination [5]. The differentiation between obsessive thoughts and common worries is that obsessive thoughts tend to be more unrealistic and involve more imagery than common worries [6]. Moreover, individuals are often embarrassed by their obsessive and intrusive thoughts and can be reluctant to share these thoughts with their health care provider [7]. Individuals with OCD often combat their obsessive thoughts with compulsive, uncontrollable behaviors. These repetitive behaviors or cognitive acts are intended to reduce the individual’s anxiety. Common compulsions include hand washing, and checking and rigid maintenance of order and organization. Common cognitive acts include counting numbers, praying, and repeating words or phrases over and over. Much as with their obsessive thoughts, individuals with OCD are commonly embarrassed by their compulsions and recognize that they are irrational but are still unable to refrain from them. Although obsessions can occur exclusively without compulsions, it is more likely that they co-occur [8]. Individuals with OCD may also use neutralizations, which are repeated thought processes that help prevent, cancel, or reverse the feared consequences and distresses caused by their obsession [9,10]. Individuals with OCD often present with a concern that their thoughts will lead to negative consequences for themselves and/or others. An additional common trait in individuals with OCD is thought-action fusion, the belief that thinking of an event increases the probability of its occurrence and that a thought is a moral equivalent of the physical act [11,12].

Cognitive behavioral theories explain the etiology of OCD, with obsessive behaviors serving as a distraction from unpleasant thoughts [10]. It is theorized that abnormal obsessions are caused by problematic reactions to feelings of elevated responsibility, leaving the individual feeling a need to always be competent to avoid criticism. The compulsive behaviors then serve as an avoidance tactic [9,13]. These compulsions reinforce maladaptive behaviors and eventually develop to outlast the cause of the anxiety-inducing thought [14]. By using these theories and observing the effect of treatment on cognitive anxiety processes at a neural level, we can understand the etiology of OCD better.

Cognitive behavioral therapy (CBT) with exposure and response prevention (ERP) is regarded as the first-line treatment for OCD [15-20]. CBT targets thoughts and cognition, the central components of OCD [20,21]. The structure of CBT for OCD is similar to that of CBT for depression or anxiety, with the addition of ERP being the biggest difference [22-24]. Although CBT is a frontline treatment, it is costly, time consuming, and often inaccessible. Therefore, more accessible and efficient interventions must be developed without sacrificing the quality of care. Fortunately, web-based mental health interventions have become increasingly popular, and the electronically delivered CBT (e-CBT) is a feasible option [25]. Research suggests that e-CBT is an effective and feasible intervention for OCD, with results comparable with those of in-person treatment [25-30]. However, e-CBT is often implemented in nonscalable and nonsecure formats. Moreover, the efficacy of CBT, along with new and innovative treatments, can be drastically improved if we understand better how treatment affects neural anxiety processing and cognitive functioning [16-21].

The most implicated regions of the brain associated with OCD are the basal ganglia and frontal cortex. These regions are involved in motor control and cognitive functioning tasks, including abstract reasoning, planning, decision-making, and inhibition [31-33]. More specifically, the basal ganglia play a large part in selecting movements that have positive effects [34]. In the case of OCD, it is hypothesized that this could play a part in the compulsive behaviors of OCD (eg, hand washing if cleanliness is an obsession). The frontal cortex is involved in reward processing, impulse control, and emotional control, among others [35]. If we learn that treatment can alter a patient's anxiety processing at a neural level, more specific treatments targeting these brain regions can be developed. Research suggests that in patients with OCD, the basal ganglia and frontal cortex are hyperactive at rest, becoming further activated while in anxiety-inducing situations [13,15,33,36-43]. These studies also suggest that successful treatment may result in a partial reversal of this hyperactivation [13,15,33,36-43]. However, more work is needed to make definitive conclusions on whether activation levels decrease following successful treatment.

By measuring brain activation levels while exposed to neutral and anxiety-inducing stimuli pre- and posttreatment, the suspected regions involved in OCD pathology (basal ganglia and frontal cortex) can be observed. These findings can help explain whether effective treatment results in changes in activation levels, whether symptom improvement is correlated to changes in activation levels, and if there are any treatment response identifiers. If anxiety processing in patients with OCD can be understood better, more targeted treatments altering these specific parts of cognition can be developed. It is currently unknown whether e-CBT can produce these effects.

### Objectives

This study will use a 16-week e-CBT with an ERP program to evaluate the effects of treatment on activation levels in the basal ganglia and frontal cortex. Previous findings suggest that CBT may partially reduce the hyperactivation commonly observed in OCD. It is hypothesized that successful treatment will decrease activation levels in the basal ganglia and frontal cortex when comparing pre- and posttreatment levels in patients with OCD with controls. This study will aim to address the following questions:

Does successful treatment result in changes in brain activation levels in regions involved in neural anxiety processing at the core of OCD pathology?Is there a correlation between changes in symptom severity and changes in brain activation levels after treatment in patients with OCD?What is the efficacy of this e-CBT program compared with control in improving symptoms, quality of life, and levels of functioning in patients with OCD?What is the feasibility and user experience of this e-CBT program from a patient perspective?

## Methods

### Design

A nonrandomized pilot study design will be used with all participants receiving 16 weekly sessions of e-CBT. Functional magnetic resonance imaging (fMRI) will be conducted at baseline and posttreatment to evaluate activation level changes in the basal ganglia and frontal cortex. Clinically validated symptomology questionnaires will be used to evaluate treatment efficacy. In addition, qualitative interviews will be conducted to gather personal demographic information as well as information regarding participant experience while using the web-based psychotherapy clinic. The pilot study has been registered on the ClinicalTrials.gov Protocol Registration and Results System (NCT04630197). In addition, ethics approval has been obtained from the Queen’s University Health Sciences and Affiliated Teaching Hospitals Research Ethics Board (HSREB; file number 6031276).

### Participants

Participants (n=10) will be recruited from family medicine and psychiatric clinics at Queen’s University and Kingston Health Sciences Centre sites (Hotel Dieu Hospital and Kingston General Hospital) in Kingston, Ontario, Canada. In addition, local and social media advertisements will be used. Participants will be enrolled in the study based on referrals from outpatient clinics and family doctors as well as self-referrals. Those invited and interested in participating will have the study protocol explained and an evaluation done by a psychiatrist on the research team through a secured video appointment. Participants will be evaluated for a diagnosis of OCD based on the *Diagnostic and Statistical Manual of Mental Disorders, 5th Edition* [44]. After a diagnosis of OCD is confirmed and the participant is given written and verbal instructions on how to participate in the study, informed consent will be obtained.

The inclusion criteria include the following: between the ages of 18 and 65 years at the start of the study, a diagnosis of OCD according to the *Diagnostic and Statistical Manual of Mental Disorders, 5th Edition* criteria, competence to consent to participate, ability to speak and read English, and consistent and reliable access to the internet. Exclusion criteria include the following: having any metal implants or additional factors deemed not safe for an MRI scan, active psychosis, acute mania, severe alcohol or substance use disorder, and/or active suicidal or homicidal ideation. In addition, if a participant is currently receiving another form of psychotherapy, they will be excluded from the study.

### Therapy

Weekly sessions of e-CBT will be conducted through the Online Psychotherapy Tool (OPTT; OPTT Inc), a secure, web- and cloud-based mental health care delivery platform. These web-based sessions will consist of approximately 30 slides and interactive therapist videos, with 16 modules in total (1 module per week). The content and format of these web-based sessions will mirror in-person CBT for OCD. The connection between thoughts, behaviors, emotions, physical reactions, and the environment will be a focus. Moreover, mindfulness, body scanning, self-care, goal setting, thinking errors, the 5-part model, and thought records will be employed as techniques for participants. ERP will be incorporated into the e-CBT program as this is the first-line route of treatment. Slides will highlight different topics each week and include general information, an overview of skills, and homework on that topic. The homework included in each session will be submitted through OPTT and reviewed by therapists, with personalized feedback provided within 3 days of submission. Weekly homework submission for feedback will be mandatory before being eligible for the next session. After each completion of the e-CBT program, participants will be interviewed to investigate their experience using OPTT and their perceptions of how the treatment went. OPTT can be accessed from a variety of devices (ie, desktop computers, laptops, cell phones, and tablets) and internet browsers.

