### Outcomes

The primary outcome measure will be changes in activation levels of the basal ganglia and frontal cortex. This will be collected through detectable changes in BOLD values from the fMRI scans at baseline and after treatment (week 16). The secondary outcomes will be changes in symptom severity, quality of life, and functioning. Changes in symptom severity will be evaluated using clinical symptomatology questionnaires (Yale-Brown Obsessive-Compulsive Scale and Obsessive-Compulsive Inventory, Revised) [46,47]. Changes in quality of life will be measured using the Quality of Life and Enjoyment Questionnaire [48]. Changes in levels of functioning will be measured using the Sheehan Disability Scale [49]. All questionnaires will be collected directly through OPTT at baseline, after session 8, and after treatment (week 16).

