### Compliance

As with all mental health disorders, treatment compliance is always an area of focus when designing interventions. Participants will have the importance of treatment compliance explained to them during the informed consent process, and participants will need to submit their homework assignments through OPTT before gaining access to their next treatment session. From a previous meta-analysis conducted, the estimated completion rate from in-person psychotherapy is approximately 75% [50]. Additional meta-analyses found treatment adherence for web-based psychotherapy to be between 61% and 66%, with no significant difference with in-person psychotherapy [51-53]. A study investigating the efficacy of a 10-session e-CBT program for OCD had a mean completion of 7.28 sessions [54]. Previous research using OPTT indicated participants completed >8 sessions on average, with over half the participants completing all sessions. In a previous project using e-CBT for patients with generalized anxiety disorder, 90% of participants completed 10-12 weeks of the 12-week program, with over 75% of participants being retained for a 12-month follow-up [55].

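### User experience is a study question, but the only stated trigger for the experience interview is completing the programme, so early stoppers have no stated route into the answer

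*Protocol article*

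**What the plan says.** The Objectives section lists four questions. The last is "What is the feasibility and user experience of this e-CBT program from a patient perspective".

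Two places describe the interviews. The Design section says that "qualitative interviews will be conducted to gather personal demographic information as well as information regarding participant experience while using the web-based psychotherapy clinic", with no time point and no limit on who is interviewed. The Therapy section gives the time point: "After each completion of the e-CBT program, participants will be interviewed to investigate their experience using OPTT". The same section says that homework must be handed in each week before the next session opens.

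The primary outcome is activation change on fMRI. For the rest, the Outcomes section says: "The secondary outcomes will be changes in symptom severity, quality of life, and functioning". Neither the Outcomes nor the Analysis section ties any measure to the fourth question. The Compliance section reports completion and adherence figures from other studies but sets no expected rate for this one.

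**The concern.** Whether a person finishes is itself a large part of whether a programme is feasible. An interview that becomes due only on finishing therefore selects its respondents on the thing being studied. The homework step sharpens this: someone who finds the homework unworkable cannot reach the later sessions, so does not complete, and on the text as written does not reach the interview.

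The Results section says a larger randomised trial is planned after this pilot. For that trial, the reasons people stop are among the most useful things a 10-person pilot can supply. They are hard to recover later if nobody asks when people leave.

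**Working it through.** The plan gives no feasibility calculation to reproduce. Two checks apply.

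**1. Does any section bring early stoppers into the interview?**

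- Objectives: poses the question and sets no method.
- Design: interviews on experience, with no timing and no mention of people who stop.
- Therapy: interview after completion, with no other trigger.
- Outcomes: questionnaires at baseline, after session 8 and after treatment. They cover symptoms, quality of life and functioning, not experience of the programme.
- Analysis: nothing on interviews or feasibility.
- Ethics and Privacy: platform metadata and analytics, not linked to the fourth question.

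No section does.

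**2. How many of the 10 might be missed?**

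Inputs: n = 10 (Participants section) and completion rates c from the studies cited in the Compliance section. Reading each cited rate as the share who complete all 16 sessions here is an assumption. The figures describe other programmes, and some describe adherence or near-completion.

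Expected number not completing = 10 × (1 − c). Chance of at least one = 1 − c^10. Chance of three or more = upper binomial tail with n = 10 and probability 1 − c.

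| Cited figure | c | Expected non-completers | At least one | Three or more |
|---|---|---|---|---|
| Same platform, over half completed all sessions (lower limit) | 0.50 | 5.0 | 99.9% | 94.5% |
| Web-based adherence, lower | 0.61 | 3.9 | 99.3% | 81.6% |
| Web-based adherence, upper | 0.66 | 3.4 | 98.4% | 71.6% |
| In-person completion | 0.75 | 2.5 | 94.4% | 47.4% |
| Earlier e-CBT project in generalised anxiety | 0.90 | 1.0 | 65.1% | 7.0% |

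Example: at c = 0.61, 10 × 0.39 = 3.9 and 1 − 0.61^10 = 1 − 0.0071 = 0.993.

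The 90% figure counts people who finished 10 to 12 weeks of a 12-week course, so full completion there may have been lower. The article also cites a mean of 7.28 of 10 sessions in another OCD programme. That is an average number of sessions, not a share of people completing, so it is not used.

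The cited figures span about 1 to 5 missed participants out of 10. Even at the most favourable rate, at least one missed participant is more likely than not.

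**The case against.** The strongest reply is that the Therapy sentence fixes a time, not an exclusion. The authors may have meant the end of the 16 weeks for everybody, and the Design section describes the interviews without restriction. This stands in part. The article nowhere says that people who stop will be refused an interview, and a reader who infers a deliberate exclusion goes beyond the text. But the only stated trigger is one that a person who stops never reaches. If the authors meant everyone, one sentence would settle it.

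A second reply is that a journal article leaves interview procedures to the full protocol. That covers interview guides and coding methods. It does not cover a stated trigger that decides who is interviewed.

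A third reply is that feasibility data are not lost. Homework passes through the platform and controls access to each session, so session completion can be counted for everyone enrolled. This stands. What is at risk is the views of those who stop. The countable measures exist but are not named as the answer to the fourth question.

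Finally, this is the last of four questions, descriptive and qualitative, in a small pilot. That limits the weight of the point but does not remove it.

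**Conclusion.** The point holds in a limited form. Read as written, the user-experience answer would come from completers only. It would probably be too favourable and would lack the reasons for stopping. The direction rests on the assumption that dissatisfaction or difficulty contributes to stopping. The size, about 1 to 5 of 10 participants, rests on carrying other studies' rates over to this trial.

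Three stronger readings are not supported:

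- *A measured overstatement of acceptability.* The plan does not propose to estimate a proportion who find the programme acceptable, and the documents give no acceptability rates for completers or non-completers. No size of bias can be derived.
- *Loss of demographic covariates for people who stop.* The Design section assigns demographic information to interviews but does not place its collection after treatment. Age has to be known at entry for the 18 to 65 criterion, and a psychiatrist evaluates each participant before consent.
- *Silence from everyone whom treatment did not help.* Completers whose symptoms do not improve would still be interviewed. The gap concerns those who stop early.

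The primary fMRI outcome and the questionnaire outcomes are unaffected. The change should be made because the missing views cannot easily be collected afterwards.

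**What to change.** Change the Therapy sentence so that every enrolled participant is invited to the experience interview at week 16 or on stopping, whichever comes first. The week-16 limb also reaches anyone who has fallen behind on modules but has not formally stopped. Report how many were invited, how many took part and how many declined, separately for completers and those who stopped.

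In the Outcomes section, name the feasibility measures for the fourth question: sessions completed out of 16, the proportion completing all 16, and the proportion with two usable scans. Count each over all enrolled, from platform and scan data the study will hold anyway.

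The cost is a few more short interviews (about 1 to 5 on the cited rates) and a few lines of text. Sample size, treatment and the homework rule stay as they are. The drawback is that some who stop will decline, so the gap narrows rather than closes. Reporting the number who decline lets the reader judge what remains.

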### Imaging

All imaging will occur at the Queen’s University MRI Facility in Kingston, Ontario, Canada, using a Siemens 3.0 Tesla whole-body MRI scanner with a standard coil. Scans will occur at baseline (pretreatment) and after week 16 (posttreatment). During scanning, participants will lie on the scanning table on their backs, with their heads resting on a foam pad to reduce movement. Scanning appointments will take approximately 1 hour per session.

Anatomical reference images will be captured initially. After this, fMRI scans will occur while participants are shown neutral images and anxiety-inducing images (eg, dirty dishes if cleanliness is an anxiety-inducing concept for a specific participant). The frontal cortex and basal ganglia will be the focus of the imaging procedures as their activation level changes during neural anxiety processing are of interest. These images will be standardized pictures from the International Affective Picture System [45]. This large database allows for the selection of images that relate to a variety of obsessions representative of each participant (ie, contamination, sexual thought intrusion, and fear of harm). Each set of pictures will be individually tailored to each participant. These images will be selected ahead of time by a psychiatrist on the research team and will be related to the participant’s anxieties. Participants will be shown a total of 40 images (20 neutral and 20 anxiety inducing; R=0.5) during the fMRI sessions. There will be four fMRI runs that occur in the following sequence:

5 neutral images (30 seconds per image, 5 seconds break between), 1-minute break, 5 anxiety-inducing images (30 seconds per image, 5 seconds break between), 1-minute break.5 new anxiety-inducing images (30 seconds per image, 5 seconds break between), 1-minute break, 5 new neutral images (30 seconds per image, 5 seconds break between), 1-minute break.5 new anxiety-inducing images (30 seconds per image, 5 seconds break between), 1-minute break, 5 new neutral images (30 seconds per image, 5 seconds break between), 1-minute break.5 neutral images (30 seconds per image, 5 seconds break between), 1-minute break, 5 anxiety-inducing images (30 seconds per image, 5 seconds break between).

The images will be shown in sets (groups of 5 images) as opposed to intermingled, in the hope of producing a more sustained emotional state and allowing for more distinct readings. The ordering of the image sets repeats halfway through (back to back of the anxiety-inducing images in the example above) to control for participants becoming accustomed to image ordering. This ordering will be changed for every participant (ie, the next participant would receive back-to-back sets of the neutral imaging in runs 2 and 3) to counterbalance the imaging sets. Participants will be prompted to imagine themselves in the situations described in the images. The images will appear on a screen that will be reflected into the scanner for participants to view. A 0.5% blood oxygen level–dependent (BOLD) signal difference between conditions (*P*<10^-6^) will be considered a detectable change (eff=0.005).

Anatomical reference images will be captured with the phase-encoding direction collected sagittally from anterior to posterior. These images will be captured with T1-weighted high-resolution magnetization-prepared rapid acquisition gradient-echo (MPRAGE) images with 0.8×0.8×0.8 mm^3^ isotropic voxels. These images will use a 256 mm field of view (FOV), 2500 ms repetition time (TR), 2.22 ms echo time (TE), 8-degree flip angle, and a 320×320 mm matrix resolution. Following this, T2*-weighted gradient-echo echo-planar imaging (GE-EPI) with 3.0 mm 3.0×3.0×3.0 mm^3^ isotropic voxels will be used for the stimuli-exposed image acquisitions in an anterior-to-posterior direction. These images will use a 192 mm FOV, 2500 ms TR, 28.4 ms TE, 90-degree flip angle, and a 64×64 mm matrix resolution. A multiband acceleration factor of 2 will be used, with 170 volumes being captured. Following the GE-EPI imaging, two short spin-echo field map scans will be captured from anterior to posterior and then posterior to anterior. These images will use a 192 mm FOV, 8000 ms TR, 66.0 ms TE, 90-degree flip angle, 180-degree refocus flip angle, and a 64×64 mm matrix resolution. All images will use a bandwidth of 1500 Hz.

The GE-EPI fMRI data will be mapped to a nondistorted set of gradient-echo images from the same participant to undistort the images. Next, the nondistorted gradient-echo images will be mapped onto the T1-weighted MPRAGE image. Finally, the T1-weighted MPRAGE will be mapped to the Montreal Neurological Institute standardized brain template. In doing this, the GE-EPI fMRI data will be mapped to the Montreal Neurological Institute template with maximum accuracy.

